## Abstract

**Background:**

Traumatic brain injury (TBI) in children is associated with a range of poor long-term outcomes, including behavioural disturbances. Parents can experience high levels of stress and injury-related burden, and evidence suggests that distressed parents are less likely to adopt positive parenting styles to manage their child’s behaviour. The ‘Signposts for Building Better Behaviour’ program is a parenting programme that was originally developed to assist parents of children with an intellectual disability in managing their child’s behaviour. More recently, it has been adapted to include a TBI module, to assist parents in managing post-TBI behaviour. However, geographical and financial barriers remain, preventing many parents from accessing the programme in the standard face-to-face modality. This project aims to investigate the feasibility and acceptability of the programme when delivered with clinician support via videoconferencing.

**Methods/design:**

The sample for this feasibility study will be recruited from the Royal Children’s Hospital, Melbourne, and the Victorian Paediatric Rehabilitation Service. Participants will be the parents of a child who sustained a TBI between the ages of 2.0 and 6.11, within the previous 2 years. The parents of 15 children will complete the programme, with clinician support via videoconferencing, while the parents of a further 15 children will form a treatment as usual wait-list control group. Parents complete questionnaires assessing their child’s behaviour, as well as assessing their own mental health, sense of parenting competency, disciplinary style, and family functioning. These will be completed upon enrolment in the study regarding their child’s pre-injury behaviour and then again pre-intervention, immediately post-intervention, and 4 months post-intervention. Parents who complete the intervention will also complete questionnaires assessing their satisfaction with the programme and its delivery. Information will be collected on the feasibility, clinical practicality, and acceptability of the programme when delivered through this medium.

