### Study aims

The primary aim of the current study is to investigate the feasibility and acceptability of conducting Signposts with videoconferencing as the mode of clinician support. In particular, this study intends to investigate this in families where the child sustained the TBI in early childhood, an age group that may be particularly prone to post-TBI poor outcomes [35–37] but, to date, has been relatively neglected with minimal attention directed to development of age-appropriate evidence-based interventions targeting behaviour problems.

More specifically, the study objectives are to:Investigate the feasibility of delivering the programme with clinician support via videoconferencing, with the goal of developing a larger RCT. This will be investigated with the collection of data on sample retention rates, participant programme adherence, and duration to reach target sample size.Collect information to inform on the clinical practicality of delivery through this medium, including the duration of videoconference sessions, rate of technology difficulties that cause disruption to sessions, and the time frame for programme completion (in weeks).Explore the acceptability of the programme when delivered through this medium, with completion of a consumer satisfaction survey, as well as by enquiring on the participant’s comfort with using the technology. It is expected that, consistent with programme delivery through different modalities, the programme will have a high level of consumer satisfaction in this population when delivered with clinician support via videoconferencing.Explore preliminary clinical outcomes across those who completed the programme compared with those on a wait-list, in order to inform likely efficacy estimates for a fully powered RCT. Primary measures will assess child behaviour, while secondary outcome measures will assess parent distress, parenting disciplinary style, parenting sense of competency, and family functioning. These will be measured using questionnaires considered standard for research involving the Signposts programme (see, for example, Woods and colleagues [23]). It is expected that those who complete Signposts will report reductions in post-TBI child behaviour problems, parental distress, and dysfunctional parenting, while increasing family functioning and parental sense of competency.

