#### Programme satisfaction

Parent satisfaction with the Signposts programme, and its delivery, will be measured using the nine-item Consumer Satisfaction Scale (CSS), which was developed for the purpose of investigating satisfaction with the Signposts programme [18]. Items on this measure are recorded on a five-point Likert scale, in which participants indicate their level of agreement with a statement about their experience with the programme, from ‘Strongly Disagree’ to ‘Strongly Agree’.

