#### Data collection

Data will be recorded to capture the number of eligible parents approached, the number who consented to the programme, and the number who successfully completed the programme, as well as reasons for non-participation and non-completion.

Questionnaires will be administered using a secure online data collection instrument (RedCap), with parents sent web links at the appropriate time points. Upon enrolment in the study, parents will be sent the web-link questionnaires and asked to complete the outcome measure questionnaires retrospectively, reporting on their child and family’s functioning prior to the TBI. It is acknowledged that this may be vulnerable to parent reporting bias, particularly where children are several years post-injury. However, evidence suggests that post-TBI behavioural problems may not emerge or present for intervention until several years post-injury [10, 11], which means that including families several years post-injury more closely mirrors the clinical setting. It therefore seems reasonable to include such families in this feasibility study. Future research may aim to minimise this bias by reducing the eligible time since injury.

Prior to commencing the programme, approximately 1 month following initial questionnaire completion, parents will be asked to complete the measures again with regard to their family and child’s *current* functioning. Outcome questionnaires will again be sent in the form of web links via email immediately after the intervention and 4 months post-intervention. The approximate timeline for completion of these questionnaires is summarised in Table 2.

**Table 2 Tab2:** Summary of measures used

Construct	Measure	Time point			
		1	2	3	4
Socioeconomic status	Social Risk Index	●			
Outcome measures					
Child behavioural outcomes	Child Behavior Checklist	●	●	●	●
Family outcomes	McMaster Family Assessment Device	●	●	●	●
Parental functioning					
Parental psychological distress	Depression Anxiety Stress Scales	●	●	●	●
Confidence and satisfaction in the parenting role	Parenting Sense of Competence Scale	●	●	●	●
Disciplinary practices	Parenting Scale	●	●	●	●
Programme satisfaction	Consumer Satisfaction Scale			●^a^	

Time point 1 = retrospectively completed about pre-injury behaviour, 2 = pre-intervention, 3 = post-intervention, 4 = 4 months post-intervention

^a^Intervention group only

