### Data analysis

Frequencies and percentages will be used to describe the population across key demographic and injury variables. We will compare the intervention and wait-list control groups across key variables (age at injury, injury severity, social risk, pre-injury behaviour, and pre-intervention behaviour) to detect any significant difference which may later compromise the generalisation of the findings.

Investigating the feasibility, clinical practicality, and acceptability of Signposts with videoconferencing support will be exploratory in nature. The objective is to collect information on ease of use, participant satisfaction, homework completion rates, programme completion and adherence, and attrition rates. Rates of programme attrition will be reported, as well as consumer satisfaction with the programme (reported as mean scores and percentages for items on the CSS).

To examine preliminary data on the impact of the programme on key outcome areas, we will compare the post-intervention scores on the CBCL scales, FAD, DASS, PS, and PSOC across the intervention and control groups and will report the mean and standard deviation of each group across these measures. To report preliminary findings on the maintenance of any treatment effects, means and standard deviations will be reported to assess any change within the intervention group from post-intervention to 4-month follow-up across the CBCL scales, FAD, DASS, PS, and PSOC. These findings may inform efficacy estimates for a larger RCT.

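### If, as the Abstract words it, only parents who complete the intervention answer the satisfaction scale, the results describe those who stayed and may overstate acceptability; Table 2 words the group differently.

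*Protocol article*

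**What the plan says.** The Study aims section makes acceptability part of the main purpose: "The primary aim of the current study is to investigate the feasibility and acceptability of conducting Signposts with videoconferencing as the mode of clinician support". It is to be explored "with completion of a consumer satisfaction survey, as well as by enquiring on the participant’s comfort with using the technology". The stated expectation is that "the programme will have a high level of consumer satisfaction in this population when delivered with clinician support via videoconferencing"; no numerical threshold is attached.

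The Programme satisfaction section says satisfaction "will be measured using the nine-item Consumer Satisfaction Scale (CSS"), with five-point agreement items.

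On who answers, the article has two wordings. The Abstract (Methods/design) says: "Parents who complete the intervention will also complete questionnaires assessing their satisfaction with the programme and its delivery". Table 2, under Data collection, places the CSS at time point 3 only, with the footnote "Intervention group only". Table 3 puts the post-intervention questionnaires in week 11, one week after the fifth and last videoconference.

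For parents who do not finish, the Data collection section records how many were approached, consented and completed, "as well as reasons for non-participation and non-completion". The Data analysis section reports attrition together with "consumer satisfaction with the programme (reported as mean scores and percentages for items on the CSS"). It names no denominator for those percentages.

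**The concern.** The new element under study is support by videoconference. Parents who leave because that format does not suit them are among the most informative about acceptability. If the scale is offered only to those who finish, their views enter the results as a reason for stopping at most, never as a score. The item means and percentages would then come from a group selected partly by the property being measured, and the likely direction of that selection is upward.

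This matters because the study is meant to inform a larger randomised trial. A satisfaction figure taken from completers, read as the view of all families offered the format, could make the format look more acceptable than it is. In an arm of 15, a handful of early stoppers is enough to shift the result.

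**Working it through.** **The passages side by side.**

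- Abstract: the satisfaction questionnaires belong to parents who complete the intervention.
- Table 2 footnote: the CSS belongs to the intervention group. This separates the two arms and does not itself exclude non-completers.
- Tables 2 and 3: a single administration, after the last session. A parent who stops in, say, week 4 has no CSS assessment tied to stopping.
- No section says that a parent who stops early is sent the scale.

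Followed as the Abstract words it, the plan yields a completer-only measure. Followed as the footnote words it, it could cover everyone in the arm. The text does not settle which.

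**Size.** The plan gives no figure to reproduce: it states no expected attrition and no expected satisfaction level. The only input from the documents is the arm size of 15 (Sample size section). Let k be the number who stop early, C the satisfaction among completers and D the satisfaction among those who stop.

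- Completer-only result: C
- All-starter result: [(15 − k) × C + k × D] / 15
- Difference: (k/15) × (C − D)

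The largest shift per dropout occurs at C = 100% and D = 0%: 1/15 = 6.7 points. The difference is zero if k = 0 or C = D.

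**Illustration.** C = 90% for one CSS item is an assumption, as are k and D. The table gives the all-starter percentage, with the excess of the completer-only 90% in brackets.

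| k | D = 90% | D = 50% | D = 20% | D = 0% |
|---|---|---|---|---|
| 1 | 90.0 (0) | 87.3 (2.7) | 85.3 (4.7) | 84.0 (6.0) |
| 3 | 90.0 (0) | 82.0 (8.0) | 76.0 (14.0) | 72.0 (18.0) |
| 5 | 90.0 (0) | 76.7 (13.3) | 66.7 (23.3) | 60.0 (30.0) |

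One cell in full, k = 3 and D = 20%: (12 × 90 + 3 × 20)/15 = 1140/15 = 76.0, an excess of 14.0 points.

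The same holds for item means. With an assumed completer mean of 4.5 and dropout mean of 2, the all-starter mean is (14 × 4.5 + 2)/15 = 4.33 for k = 1, (12 × 4.5 + 6)/15 = 4.00 for k = 3, and (10 × 4.5 + 10)/15 = 3.67 for k = 5.

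Under these assumptions the excess runs from 0 to 30 points for 0 to 5 dropouts. That is a range of possibilities, not an estimate for this trial.

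**The case against.** The strongest reply is that the article uses the word complete loosely, as a label for the intervention arm. The Abstract has the parents of 15 children completing the programme, and 15 is the whole arm. The Overall study design section also describes the arm as one in which the programme is completed and contrasts its completers with the wait-list. On that reading the Abstract sentence only says that wait-list parents are not asked, which agrees with the Table 2 footnote. Table 3 is described as approximate, and a condensed article may leave the handling of early stoppers to the full protocol. This stands to the extent that a completer-only rule is not proven to be intended. It does not remove the problem: the sentence as printed restricts to completers, the timing fits that restriction, and nothing printed extends the scale to those who stop.

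Second, the CSS is not the only evidence on acceptability. Comfort with the technology and ease of use are also collected, and attrition with reasons for non-completion is recorded. A format that many families rejected would show up as attrition next to the satisfaction results. This stands as real mitigation, but none of it gives a satisfaction score for a parent who stopped.

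Third, a reader might infer that acceptability is certain to be overstated, that high satisfaction is guaranteed by the design, or that the study cannot answer its acceptability question. The documents do not support any of these. Bias needs dropouts who are less satisfied than completers, and parents may stop for unrelated reasons. The analysis is described as exploratory, with no threshold or test to pass. Nor is there a planned overall percentage satisfied: results are reported item by item on nine items. An example that scores every dropout as dissatisfied is therefore a bound, and partly counts attrition a second time.

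**Conclusion.** The point holds in a conditional form. The Abstract and the Table 2 footnote describe the CSS respondents differently, and the only scheduled administration follows the last session. If only completers answer, the CSS describes those who stayed and may overstate acceptability, which is part of the primary aim.

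The size is (k/15) × (C − D): no more than 6.7 points per dropout, and nil without dropouts or without a satisfaction gap. Any single figure rests on attrition and satisfaction values that the documents do not give. Reporting attrition and reasons for stopping limits the harm but does not replace the missing scores. This is a modest design weakness, cheap to correct before the data are collected.

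**What to change.** Make the Abstract and Table 2 say the same thing, and state explicitly what happens when a parent stops early:

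1. Send the CSS web link to every intervention parent who started the programme and had at least one videoconference session, at the time of stopping or at time point 3. Parents who attended only the introductory interview cannot rate videoconference support. Show them as a separate count among the starters.
2. Report each CSS item with the number of responders out of all starters, and show completers separately.
3. Add one sensitivity line that counts non-responders as not satisfied, labelled as a lower bound. This requires stating beforehand which item responses count as satisfied.

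The questionnaires already go out as web links, so the cost is a few extra links and some reporting text. The downsides are some non-response among parents who have left and a possibly less favourable figure.

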**Discussion:**

This study is the first to investigate the feasibility of delivering post-child TBI behavioural intervention via videoconferencing in Australia. Preliminary findings from this study may support the development of a larger randomised controlled trial. It is hoped that programme delivery through this medium would facilitate better access to the programme, enabling improved long-term outcomes for families.

**Trial registration:**

ANZCTR, ACTRN12616001574437

## Background

### Child behavioural outcomes post-TBI

Paediatric traumatic brain injury (TBI) is a leading cause of disease burden in young children [1] and is associated with a range of poor psychological outcomes [2]. This includes post-injury behaviour changes [3], which can include excessive externalising behaviour, where the child demonstrates aggression, non-compliance, and irritability [4, 5]. The child may also exhibit poor self-regulation [6] and behave inappropriately in social settings [7, 8]. Internalising behaviours may also be present, in which the child is withdrawn and anxious [3], and parents may report personality changes [9].

The prevalence of such changes have been documented in 36% of severe TBI cases and 22% of moderate TBI cases [10]. Research also suggests that young children who experience a mild TBI requiring inpatient care are more likely to have behaviour problems than their uninjured peers [11]. Indeed, Catroppa and colleagues [12] showed that behaviour problems can emerge regardless of injury severity. These changes have been demonstrated to emerge early post-injury and increase over time [10] and may persist in the long-term [10, 11]. Behaviour disturbances post-injury have the potential to set individuals on a poor long-term trajectory, which may include difficulties in the classroom [10], anti-social behaviour [4], and increased risk of criminality [13]. Thus, problematic behaviour post-TBI is an outcome which requires attention and cannot be assumed to resolve without intervention.

### Parent outcomes when caring for a child post-TBI

Parental stress and family burden are also elevated following a child TBI. More specifically, behaviour disturbances post-TBI have been demonstrated to relate to higher parent distress and greater injury-related family burden [10]. Evidence suggests that this relationship is bi-directional, where parental distress, and mental health more generally, also uniquely predicts child behaviour problems [14]. Parents exhibiting greater distress are suggested to be less likely to adopt positive parenting styles to manage their child’s behaviour [15]. Relatedly, poorer parental communication [16] and disciplinary practices [17] relate to poorer post-TBI outcomes. Therefore, interventions which aim to reduce parent distress, and improve parental disciplinary styles and family functioning, may be particularly beneficial in improving post-paediatric TBI behaviour.

### The Signposts for Building Better Behaviour programme

‘Signposts for Building Better Behaviour’ (Signposts) is an intervention programme initially developed to assist parents in managing challenging behaviours in children with intellectual disability [18], with the additional aim of decreasing parent distress and increasing their sense of competence in managing their child’s behaviour. Signposts is a manualised programme in which parents read modules, watch videos, and complete homework exercises. Drawing on principles from behavioural therapies such as positive behaviour support, the programme aims to teach parents to conduct a functional analysis of a target behaviour, then design and implement an intervention to replace this behaviour with more desirable behaviour. The role of the Signposts therapist is to reiterate key messages from the module, answer any questions that the parent may have, and troubleshoot homework difficulties. The programme was designed to be delivered in a variety of modes of delivery, including a group format, as well as with clinician support via telephone, or in a self-directed manner (i.e. without the support of a clinician). However, research has suggested that those who receive support from a clinician during the programme are more likely to successfully complete the full programme [19].

Signposts has more recently been adapted to be relevant for parents of children with a TBI, with the inclusion of an additional paediatric TBI psycho-education module [20]. The modified programme was found to have high levels of consumer satisfaction for the parents of children with a TBI, who found the modules and the skills taught to be relevant and useful [21]. Parents reported significant reductions in challenging child behaviours, as well as significant reductions in dysfunctional parenting practices, stress, and family burden, when completing the programme through both group support and telephone support practices [22]. Evidence suggests good maintenance of these effects in the long-term post-intervention [23].

### The use of technology in delivering health interventions

Electronic health services, or ‘eHealth’, commonly refer to the ‘use of information technology in the delivery of health care’ [24]. Several studies report efficacy in the use of eHealth as a medium for delivering post-TBI behaviour interventions to families, including research utilising psycho-education and web-based family-oriented therapy, with associated improvements in caregiver distress [25–27].

The use of the Internet to deliver therapy for post-paediatric TBI behavioural disturbance has many benefits. Videoconferencing may be beneficial as parents would not require transport or childcare and could potentially avoid time taken from work to attend face-to-face therapy sessions [28]. Paediatric TBI causes a considerable degree of financial strain for families [29], and any method for alleviating this strain is worth investigating. Furthermore, the risk of sustaining a paediatric TBI is increased for those who live in remote areas [30], highlighting the need to increase access to interventions for those who live far from rehabilitative services.

While receiving telephone support for post-TBI rehabilitation can assist in removing some of these socioeconomic and geographical barriers, videoconferencing has several additional benefits [31]. Video technology means improved ability to detect non-verbal cues and provides an opportunity for including more than just one parent in the session. It enables shared viewing of programme materials such as videos, graphics, and homework exercises—none of which is possible via a traditional telephone. While videoconferencing is relatively new to post-paediatric TBI care, research in the related area of mental health intervention reports that videoconferencing has a comparable level of efficacy when compared to standard face-to-face delivery. For example, one randomised controlled trial comparing therapy across these modes of delivery found that post-therapy, 74.3% of patients treated via videoconferencing showed a reliable improvement in symptoms, compared to 75% when treated face to face [32]. Further, researchers have found there to be no significant difference between the two modes of delivery regarding the quality of the therapeutic alliance when rated by the client (*p* = 0.53) or the therapist (*p* = 0.60), or regarding client ratings of service satisfaction (*p* = 0.77) [33]. Several studies have reported that videoconferencing is more cost effective than standard face-to-face care delivery [34].

